### Inclusion Criteria

The inclusion criteria are as follows:

Men and women;>18 years of age;Use of antimalarials for at least 30 days before inclusion in the study;Diagnosis of IMRD (according to the criteria of the American College of Rheumatology or European League Against Rheumatism), rheumatoid arthritis [43], systemic lupus erythematosus [44], Sjögren's syndrome [45], systemic sclerosis [46], inflammatory myopathies [47], and mixed connective tissue disease [48];Diagnosis of osteoarthritis (subgroup) [49];Diagnosis of chikungunya-related arthropathy (subgroup).

### Exclusion Criteria

The exclusion criteria, which apply to both patients and controls, are as follows:

Previous use of chloroquine or equivalent that was not in the past 6 months;History of solid organ or bone marrow transplantation;Neoplasm of solid organs or lymphatic or myeloproliferative lineage in the past 12 months with or without adjuvant chemotherapy;Positive HIV status, regardless of highly active antiretroviral therapy;Use of intravenous human immunoglobulin in the past 30 days;End-stage renal disease on peritoneal dialysis and hemodialysis.

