**Objective:**

We present the protocol for a research project that compares the potential protective effect of antimalarials in preventing moderate-to-severe forms of COVID-19 in two groups: (1) patients treated chronically with antimalarials for rheumatic diseases and (2) other members of the patients’ household who have not been diagnosed with rheumatic diseases and are not taking antimalarials.

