### Objectives

Our primary aim is to assess the potential preventive effects of antimalarials in reducing the incidence of moderate-to-severe forms of COVID-19 in patients with rheumatic diseases. Secondarily, we aim to determine the frequency of SARS-CoV-2 infection in patients with rheumatic diseases who are chronic users of antimalarials. For both objectives, patients with rheumatic diseases will be compared with members of their household who are not taking antimalarials.

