### Sample Size

Considering a moderate-to-severe COVID-19 rate as the dependent variable, a rate which the current literature estimates to be 20% [4,6,10-18,40-42] as well as the proportion of 1 case for every 2 controls, the sample calculation was approximately 3000 antimalarial users and 6000 nonusers, with an error α=5% and β=20%.

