### Control Group

The control group will consist of healthy individuals aged >18 years, who are household cohabitants or work colleagues of patients with rheumatic diseases in the intervention group.

Contact with a suspected or confirmed case of COVID-19 is defined as an individual sharing accommodations with a patient with a rheumatic disease (eg, residing in the same house or environment as roommates, occupational colleagues, etc). The exposure grade assessment is individualized, considering the type of environment and the exposure time.

For each case, two household and/or professional contact individuals will be selected as controls. The choice of the first control is prioritized by flu-like symptoms and defined as the “symptomatic group,” including suspected or confirmed cases. Those without symptoms will comprise the “asymptomatic group;” both household and/or contact individuals can be selected, preferably paired for age and sex.

The household and/or workplace contacts were chosen to characterize the control group because of their high epidemiological value during community viral transmissions worldwide, instead of including nonusers of antimalarials with rheumatic diseases. Moreover, lupus patients without antimalarial treatment are quite uncommon, except in those with previous toxicity (maculopathy, allergy, long-term remission, etc).

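### One antimalarial exclusion serves both groups: for controls it works in the wrong direction, admitting people who stopped within 6 months as unexposed

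*Protocol article*

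**What the plan says.** The list in Exclusion Criteria opens by stating its scope: "The exclusion criteria, which apply to both patients and controls, are as follows". Its first item is "Previous use of chloroquine or equivalent that was not in the past 6 months".

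Four other places bear on antimalarial exposure:

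- **Inclusion Criteria** (patients): "Use of antimalarials for at least 30 days before inclusion in the study".
- **Abstract, Objective**: the comparison group consists of household members who "have not been diagnosed with rheumatic diseases and are not taking antimalarials".
- **Objectives**: "patients with rheumatic diseases will be compared with members of their household who are not taking antimalarials".
- **Control Group**: "The control group will consist of healthy individuals aged >18 years, who are household cohabitants or work colleagues of patients". That section sets no condition on antimalarial use, past or present.

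Sample Size calls the two groups antimalarial users and nonusers, without defining a nonuser.

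**The concern.** Antimalarial exposure is the contrast under study, so the control group should be free of recent exposure. A washout rule normally removes people with recent use and tolerates use long ago. Applied to controls, this item does the reverse. The other two items in the list that carry a time window (neoplasm, 12 months; intravenous immunoglobulin, 30 days) both exclude recent events, so the antimalarial item stands out.

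If recently treated contacts enter as nonusers and still carry some drug effect, the two groups become more alike than their labels say. A real effect on moderate-to-severe COVID-19 would then be understated, and a null result would be harder to interpret.

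**Working it through.** **1. The rule applied to a control.** I read the item by date of last use and set it beside the other sections.

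| Control's history | Exclusion Criteria | Objective / Objectives | Result |
|---|---|---|---|
| Never used | not excluded | allowed | eligible, unexposed |
| Stopped more than 6 months ago | excluded | allowed | out |
| Stopped within 6 months | not excluded | allowed (not a current user) | eligible, counted as unexposed |
| Using now | not excluded | barred | out, through the Objectives only |

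The third row is the gap. The bar on current use is in the present tense and does not reach someone who has already stopped. It is also worded for household members, whereas Control Group admits work colleagues too.

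**2. The rule applied to a patient.** The inclusion criterion asks for 30 days of use before inclusion and does not say how recent that use must be. An exclusion of people whose use ended more than 6 months ago fits that criterion. Reversing the item for both groups, so that it excluded use in the past 6 months, would remove the chronic users whom the study is about.

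**3. The plan's own figure.** The only planning figure is about 3000 users and 6000 nonusers, at α = 5% and β = 20%, with a 20% event rate. No effect size is given, so it cannot be reproduced forward. It can be back-solved with the usual two-proportion formula, 1:2 allocation, two-sided:

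n(users) = [1.96·√(1.5·p̄(1−p̄)) + 0.842·√(p₁(1−p₁) + p₂(1−p₂)/2)]² / (p₂−p₁)²

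With p₂ = 0.20 and p₁ = 0.1755, p̄ = (0.1755 + 2×0.20)/3 = 0.1918 and n = 3010. The stated size therefore corresponds to about 17.55% in users, a risk ratio of 0.1755/0.20 = 0.88. The point about the exclusion does not depend on this figure.

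**4. Dilution of the risk ratio.** Let q be the share of controls who stopped recently and still carry the users' full risk reduction throughout follow-up. The documents give no value, so q is an assumption. Then

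observed RR = RR / [(1−q) + q×RR]

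| True RR | q = 5% | q = 10% | q = 20% |
|---|---|---|---|
| 0.70 | 0.70/0.985 = 0.71 | 0.70/0.97 = 0.72 | 0.70/0.94 = 0.74 |
| 0.50 | 0.50/0.975 = 0.51 | 0.50/0.95 = 0.53 | 0.50/0.90 = 0.56 |

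**5. Dilution of power at the planned size.** With 3000:6000 and 17.55% in users, the control rate becomes (1−q)×0.20 + q×0.1755. Power is 79.9% at q = 0, 79.1% at 1%, 75.8% at 5% and 71.3% at 10%.

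**6. What q means in people.** Results gives 10,443 enrolled, of whom 5166 are patients. If the remaining 10,443 − 5166 = 5277 are all controls, q = 1% is about 53 people, 5% about 264 and 10% about 528.

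**The case against.** The strongest reply is that the item is a patient criterion placed under a heading that extends it to controls. On that view the remaining gap is narrow. Controls must be healthy and, by the Abstract, without a rheumatic diagnosis, which removes the indications that the study covers. They are called nonusers, and concomitant medications are both recorded and named as an adjustment variable. Only a healthy contact who took an antimalarial within 6 months and stopped before enrolment slips through, and nothing suggests that this was common.

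Much of this stands. A reader might infer that the item is simply worded backwards and should be reversed. The documents do not support that: the item is coherent for patients, and a plain reversal across both groups would exclude the exposed cohort. A reader might also infer a serious bias that grew with antimalarial use during the pandemic. The article gives no rate of use among contacts, and its Discussion names a possible hydroxychloroquine shortage. Nor is dropping long-past users from the controls shown to bias anything. It brings controls closer to never-users.

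What the reply does not remove is the stated scope. The article extends the item to controls in so many words, and no other section excludes recent former use. Adjustment for concomitant medication would not clearly capture a drug that had already been stopped.

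**Conclusion.** The point holds in a limited form. As an eligibility rule for controls, the item works in the wrong direction: followed literally, it classes recent former users as unexposed. This is a rule that the article states, not a detail left to a fuller document.

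Any resulting bias is toward no difference. Its size cannot be derived from the documents. It is probably small: even if 5% of controls carried the full effect for the whole of follow-up, a risk ratio of 0.70 would move only to 0.71. The loss of power is more visible (about 4 percentage points at 5%), but only for the modest effect implied by the planned sample size. All these figures rest on an assumed q and on a residual effect that does not fade. A fading effect would make them smaller.

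Controls who start an antimalarial during follow-up are a separate matter and form no part of this point.

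**What to change.** State the criterion separately by group:

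- **Patients:** keep the exclusion of lapsed users.
- **Controls:** exclude any use of chloroquine or equivalent in the 6 months before V1.

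Reconcile this with Objective, Objectives, Inclusion Criteria and Control Group, so that household and workplace controls fall under the same rule.

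Inclusion closed on May 17, so rewording alone changes no one's eligibility. Identify the affected controls from the recorded medication data. Data Collection mentions concomitant medications but does not show that use already stopped was captured in controls. If it was not, ask once at a remaining phone visit. Remove the identified controls from the primary comparison and report an analysis of all controls as sensitivity.

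If the question is asked late, controls who have died or cannot be reached will have no answer. Decide how unknown histories are handled before outcomes are examined, so that removal does not depend on outcome.

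Cost: a few lines of text, a database check, possibly one added question, and probably a few controls lost.

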### Control Group

The control group will consist of healthy individuals aged >18 years, who are household cohabitants or work colleagues of patients with rheumatic diseases in the intervention group.

Contact with a suspected or confirmed case of COVID-19 is defined as an individual sharing accommodations with a patient with a rheumatic disease (eg, residing in the same house or environment as roommates, occupational colleagues, etc). The exposure grade assessment is individualized, considering the type of environment and the exposure time.

For each case, two household and/or professional contact individuals will be selected as controls. The choice of the first control is prioritized by flu-like symptoms and defined as the “symptomatic group,” including suspected or confirmed cases. Those without symptoms will comprise the “asymptomatic group;” both household and/or contact individuals can be selected, preferably paired for age and sex.

The household and/or workplace contacts were chosen to characterize the control group because of their high epidemiological value during community viral transmissions worldwide, instead of including nonusers of antimalarials with rheumatic diseases. Moreover, lupus patients without antimalarial treatment are quite uncommon, except in those with previous toxicity (maculopathy, allergy, long-term remission, etc).

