**Figure 2 figure2:**
[figure not shown]
Telephone interview schedule.

A clinically confirmed case of COVID-19 was defined according to the Brazilian Ministry of Health criteria [50] that included self-reported symptoms (fever, cough, nasal congestion, shortness of breath, malaise, myalgia, decline in general condition, and sudden anosmia and/or dysgeusia) and/or have been in contact with someone with a confirmed or suspected case of COVID-19. A positive PCR (polymerase chain reaction) test for SARS-CoV-2, via oropharyngeal and nasopharyngeal sampling or a specific confirmatory serology (immunoglobulin G and/or immunoglobulin M), is needed to test for infection, according to the Brazilian Ministry of Health [50] (Figure 3).

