### Outcomes

Primary outcomes (at baseline and during the 24-week study period) are as follows:

SARS-CoV-2 infection (illness): suspected, suggestive, or confirmedDeathHospitalizationNeed for intensive care unitNeed for mechanical ventilationTotal hospitalization timeDate of occurrence of an adverse event (eg, death, hospitalization)

Secondary outcomes are as follows:

General clinical differences in COVID-19 course severity between rheumatic patients and nonrheumatic controls;Initial clinical differences and progression to moderate or severe course of disease between the two groups.

Confounding and adjustment variables are age, sex, comorbidities, concomitant medications, and flu vaccine.

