## Results

This study is in the data collection phase. Study recruitment opened in March 2020. In an 8-week period (from March 29 to May 17), a total of 10,443 individuals enrolled at baseline (including 5166 patients with rheumatic diseases) from 23 tertiary rheumatology centers in 97 Brazilian cities. Data analysis is scheduled to start after all relevant data have been collected.

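### Controls are partly chosen for flu-like symptoms and illness at baseline counts as a primary outcome, so an inert drug would look protective against illness

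*Protocol article*

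**What the plan says.** The two groups are recruited by different rules. For patients, Inclusion Criteria requires a qualifying diagnosis and "Use of antimalarials for at least 30 days before inclusion in the study". It sets no symptom criterion in either direction.

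For controls, the Control Group section says "For each case, two household and/or professional contact individuals will be selected as controls" and then "The choice of the first control is prioritized by flu-like symptoms". Controls chosen this way form a symptomatic group, which takes in suspected and confirmed cases. Contacts without symptoms form a second, asymptomatic group. The same section opens with "The control group will consist of healthy individuals aged >18 years", which does not fit a rule that gives priority to people who are unwell.

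The Outcomes section begins "Primary outcomes (at baseline and during the 24-week study period) are as follows", and the first item is illness, whether suspected, suggestive or confirmed. Data Collection (text after Figure 2) bases the clinical case definition on "self-reported symptoms (fever, cough, nasal congestion, shortness of breath, malaise, myalgia, decline in general condition, and sudden anosmia and/or dysgeusia" and/or contact with a case. These symptoms overlap those used to choose the first control. Statistical Analysis also takes suspected illness as an event date.

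Results reports "a total of 10,443 individuals enrolled at baseline (including 5166 patients with rheumatic diseases").

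**The concern.** A control chosen because he or she is already unwell can meet the first-listed primary outcome on the day of enrolment. Patients are not chosen that way. The illness comparison therefore starts with an excess of events among controls that has nothing to do with antimalarials, and this excess reads as protection.

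Nothing stated in the article removes it. The exclusions do not take out people who are already ill. The named adjustment variables are age, sex, comorbidities, concomitant medications and flu vaccine, with duration of illness added in Statistical Analysis. Baseline symptoms and type of control are not among them, and adjusting for the listed covariates cannot undo selection on the outcome. The limitations in the Discussion do not mention the point. This is not a detail left to a fuller plan, since the article itself fixes both the selection rule and the outcome window.

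**Working it through.** The plan states no figure for this point, so there is none to reproduce. The check asks what an inert drug would show.

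**Inputs from the article.** Two controls planned per patient, the first chosen by symptoms. Enrolled: 10,443 − 5166 = 5277 non-patients, and 5277 / 5166 = 1.02 per patient.

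**Assumptions (not in the article).** Everyone has the same probability *s* of symptoms at V1. Each patient has *m* eligible contacts, independent of each other. Later illness has probability *f* in both groups. A second control is asymptomatic where one is available.

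**Step 1, illness at V1 only.** The first control is symptomatic if any contact is: F = 1 − (1 − s)^m. With s = 5% and m = 3, F = 1 − 0.95³ = 14.3%.
- One control: RR = 5 / 14.3 = 0.35.
- Two controls: the second is ill only if all three contacts are (0.05³ = 0.0125%), so the mean is (14.2625 + 0.0125) / 2 = 7.14% and RR = 5 / 7.14 = 0.70.
- Two eligible contacts, both enrolled: the control mean is 5% and RR = 1.00. The bias vanishes when every eligible contact is taken.
- Household clustering reduces the bias. With a beta-binomial within-household correlation of 0.3 and m = 3, F = 10.8% and the one-control RR is 0.46.

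**Step 2, the outcome as written (baseline plus 24 weeks).** Risk = baseline + (1 − baseline) × f. With f = 10%:
- Patients: 0.05 + 0.95 × 0.10 = 14.5%.
- One control: 0.1426 + 0.8574 × 0.10 = 22.8%; RR = 0.64.
- Two controls: 0.0714 + 0.9286 × 0.10 = 16.4%; RR = 0.88.

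The same formulas over a range, with f = 10%:

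| s | m | RR, one control | RR, two controls |
|---|---|---|---|
| 2% | 2 | 0.87 | 1.00 |
| 2% | 3 | 0.77 | 0.93 |
| 5% | 2 | 0.77 | 1.00 |
| 5% | 3 | 0.64 | 0.88 |
| 5% | 4 | 0.54 | 0.79 |
| 10% | 3 | 0.55 | 0.85 |

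With f = 20%, s = 5% and m = 3, the figures are 0.76 and 0.93. At the enrolled numbers, if the one control is the prioritized one, a two-sided 5% test finds false protection with probability about 77% for s = 2%, m = 2, f = 10% and about 100% for s = 5%, m = 3, f = 10%.

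**Step 3, which exclusion repairs it.** Suppose people ill at V1 are removed one by one. A patient stays if he or she is well. The prioritized control stays only if all *m* contacts are well, so the remaining controls come from lower-risk households. Let household risk θ follow a beta distribution with mean 5% and correlation ρ, and let half of a 10% later risk scale with household risk, so that f = 0.05 + θ. With k = 1/ρ − 1, the mean of θ is 0.05k/(k + 1) given that the patient is well and 0.05k/(k + m) given that all contacts are well.
- ρ = 0.1 (k = 9): patients 0.095; controls 0.0909 (m = 2) or 0.0875 (m = 3). RR = 1.045 or 1.09.
- ρ = 0.3 (k = 2.333): patients 0.085; controls 0.0769 (m = 2) or 0.0719 (m = 3). RR = 1.105 or 1.18.

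Removing the individual alone thus makes an inert drug look harmful, with RR about 1.04 to 1.18. If the whole set is dropped when the patient or an enrolled control is ill at V1, both sides are conditioned on the same households, and RR is 1.00 in this model.

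**The case against.** The strongest case on the other side concerns scope and size. Objectives makes moderate-to-severe disease the primary aim and infection frequency secondary, and severe cases are those with hospitalization, ventilation or death. Recruitment is by consented telephone interview, so few people can be in hospital at V1, and a baseline window cannot sensibly apply to death. This stands as a limit. A reader might infer that the comparison of severe outcomes is distorted as strongly as the V1 illness figure of 0.35. The documents do not support that. The 0.35 ignores follow-up illness and assumes one control per patient, and severe outcomes are reached only through baseline illness that progresses. If later hospitalization were the same share of illness in both groups, its risk ratio would shift equally (0.64 in the central case), but nothing in the article fixes that share. Illness nevertheless heads the primary outcome list, so the objection does not dispose of the point.

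A reader might also infer from the ratio of 1.02 that nearly every control was a prioritized first control. Results gives totals only, and the same mean fits some patients with two controls and others with none. The ratio suggests that dilution by second controls was largely lost, but does not prove it. The description of controls as healthy also leaves unclear how strictly the symptom priority was applied.

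Finally, a true difference in risk between patients and contacts could offset the bias or add to it. That changes the observed ratio but does not remove the selection.

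**Conclusion.** The point holds for the illness outcome. Followed as written, the plan biases that comparison toward protection unless every eligible contact is enrolled, and no stated exclusion or covariate corrects this. The direction follows from the selection rule and the outcome window. The size depends on three quantities that the article does not give: symptom prevalence at V1, the number of eligible contacts and the later illness rate. Under the central assumptions the apparent risk ratio is about 0.64 with one control per patient and 0.88 with two. Clustering within households, more later illness and fuller enrolment of contacts all bring it closer to 1. The effect on hospitalization, intensive care and death is indirect, and the documents do not allow it to be quantified.

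**What to change.** Results states that analysis starts only after data collection, and COVID-19 symptoms are recorded in both groups, so the change can still be made in the analysis.

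1. In Outcomes, replace the baseline-plus-24-weeks window by new events with onset after V1, and start time at V1 in the survival analyses.
2. Restrict the primary comparison to patient-control sets in which neither the patient nor any enrolled control had suspected, suggestive or confirmed COVID-19 at V1, or stratify by household symptom status at V1. Do not remove only the ill individuals.
3. Report baseline illness and the symptomatic control group descriptively, and reconcile that group with the description of controls as healthy.

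The cost is fewer sets and fewer events in the primary comparison. Patients and controls must also be linked into sets in the analysis file, so this is somewhat more than a change of wording. No new data collection is needed.
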